**Eligibility**

Households with one or more under-5 children were eligible for the trial. Households were excluded from the first-round survey if a caregiver declined to participate in the survey. Enrolled households were registered with a distinctive identification code at the time of the first-round survey and will be followed for the next 12 months of the trial period.

***Key intervention***

Our key intervention is to activate CHV activities, and the intervention period is 1 year. The main duty of CHVs is to pay regular visits to 40 assigned households in their community and to carry out key activities mainly targeting children under five and caregivers. CHVs are required to visit 20 households every month so each participating family can receive a visit every other month. During home visits, CHVs conduct health education with key messages on sanitation and hygiene to prevent diarrhea and other infectious diseases such as hand-washing, management of diarrhea using ORS or recommended home-maid fluid, prevention of malaria including utilization of insecticide-treated nets, nutrition, breastfeeding and so on. CHVs also provide services for under-5 children to manage diarrhea with ORS and zinc and to diagnosis malaria using a thermometer and an RDT kit. CHVs will be requested to deliver all key messages applicable to the household on every home visit.

CHVs will be nominated by community committees on the basis of their literacy, volunteerism, and working experience as a volunteer in health-related fields with government, donor agencies, or non-governmental organizations. The selection criteria are based on the national CHPS guidelines, and the District Health Management Team coordinated the selection process.

The training curriculum for CHVs will be developed in reference to CHV’s training manual^35^, as recommended in the CHPS implementation guidelines. District and regional health staff will provide 5 days of training. During the 5-day training program, CHVs will learn about the concept of CHPS, their roles and responsibilities, communication skills with community members, and will gain a basic knowledge of essential maternal and child health care services as well as reporting and recording skills. After the initial training, two types of refresher training will be given. One will involve monthly meetings at the CHPS compounds with flexible topics based on the CHV’s request, and the other is a workshop to be conducted every 6 months.

A backpack, t-shirts, an identification card, a CHV certification, a digital thermometer, and stationery will be provided to CHVs. Health equipment such as ORS packets, zinc tablets, and RDT kits will be dispensed in a timely manner to assist their activities. Limited material incentives of 8.7 USD (30 CHC) worth of food items and 1.5 USD (5 GHC) worth of airtime will be also provided every month. *(The exchange rate on August 1, 2015 was applied: 1USD = 3.46 GHC.)*

The first phase, in which CHVs will be deployed in the 20 treatment communities, will last for one year.

We referred to the suggested roles in the latest CHPS implementation guidelines (draft version) and the recommended training manual for CHV training^35^ in order to specify the roles of CHVs. Table 3 summarizes the responsibilities of CHVs in the trial. The key role of CHVs is to perform home visits to assigned households in their village, and they are also required to support the community health officers (CHOs) and CHNs, to surveil major health events, to mobilize community members, and to comply with regular supervision and training.

It is critical for this trial to ensure that CHVs are properly activated in the intervention communities. The key indicators for measuring the activation level of CHVs are the frequency of their home visits, their participation in the monthly meetings, and their retention rate (Table 4).

Table 3. Job description for community health volunteers.

| **Category** | **Descriptions** |
| --- | --- |
| 1. Home visit | - Pay a home visit (minimum) once per every two months to 35 assigned households - Provide health education to the mothers and family members through constant delivery of key messages mainly regarding the prevention and management of child illnesses, family planning, hygiene and sanitation, antenatal care, postnatal care, and skilled delivery - Provide diagnostic services in malaria to under-5 children and pregnant women using a thermometer and RDT^1^ kit - Provide ORS and zinc tablets for the primary management of diarrhea in under-5 children - Provide Aquatabs to households without an appropriate source of drinking water - Provide family planning counseling to key decision-makers in the family - Support healthy behaviors of the community members (i.e. help setting ITNs^2^, referring clients to a corresponding health facility) |
| 2. Support for CHOs/CHNs | - Support child welfare clinic (CWC^3^) of CHOs^4^/CHNs^5^ in outreach and mobilize the community - Support CHOs/CHNs in referral and management of clients |
| 3. Surveillance | - Record logbook - Record Community Register for Vital Health Events - Find and report pregnancies and newborn cases |
| 4. Community mobilization and sensitization | - Participate in the community meetings and committees and raise health issues - Organize health talks at community gatherings |
| 5. Reporting and training | - Attend an initial training session for 5 days - Attend 6-month workshop sessions - Participate in monthly meeting at CHPS^6^ and report on monthly activities (a refresher session is planned as a part of the monthly meeting) - Manage the provided supplies and submit a report regarding their use |

^1^ RDT: rapid diagnostic test, ^2^ ITN: insecticide-treated net, ^3^ CWC: child welfare clinic, ^4^ CHO: community health officer, ^5^ CHN: community health nurse, ^6^ CHPS: Community-based Health Planning and Services

Table 4. Indicators for measuring the activation of community health volunteers.

| **Component** | **Indicator** | **Measurement tool** |
| --- | --- | --- |
| Service delivery | The percentage of CHVs who have visited all the assigned households (20) in the last month (among those retained) | CHV logbook at monthly meeting |
| Participation in monitoring | The percentage of CHVs who participated in the monthly meeting at CHPS more than two-thirds of the whole year | Monthly meeting minutes |
| Retention | The percentage of CHVs retained | CHO records on CHV supervision |

***Project implementation***

The Improving Maternal and Child Healthcare project in Volta Region of Ghana is being conducted in the Keta, Ketu South and Ketu North districts of from January 2014 to December 2016. The 3 project districts have a total of 24 CHPS facilities within 132 CHPS zones, with a population of 461,939, including 92,387 children under the age of 5 years. This project aims to enhance the accessibility, availability, and quality of the health services for mothers and under-5 children. In order to accomplish this goal, it provides equipment to health facilities, deploy and activate CHVs, and promotes public awareness.

The project is funded by the Korea International Cooperation Agency and implemented by a consortium of the Graduate School of Public Health, Yonsei University and the Korea International Development Institute.

***Data analysis***

Intention-to-treat analysis will be conducted to explore the effect of CHV activation on childhood infectious disease of under-five children. For diarrheal prevalence as a dependent variable, water quantity and quality, hygiene behavior of caregivers, presence of improved latrines, characteristics of the enrolled child such as age and sex, household income, and caregiver’s education level will be controlled for in quantifying the net effect of CHVs. For malaria prevalence as a dependent variable, the enrolled child’s characteristics, household income, and caregivers’ education level will be controlled. Environmental risk factors such as seasonality and altitude are also considered to be independent variables for malaria prevalence. However, the intervention and control arms in our study site present no difference in those factors so there will be no control for environmental factors. When quantifying the net effect of CHVs on child malaria prevalence, insecticide-treated bed net utilization will not be controlled since it is considered an intermediate factor between intervention and disease outcome. Generalized estimating equations will be used for investigation at the cluster level. The random effects model will be used, taking account of between-cluster variation by assuming that there are cluster-level effects. Per-protocol analysis will be performed to obtain additional background information if the overall percentage of CHVs activated does not reach 80%. Multi-level analysis will also be conducted to explore whether the effects of CHVs on child diarrheal and malaria prevalence vary by community depending on a community’s overall coverage of activated CHVs.

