***Intermediate indicators***

Intermediate indicators for the prevalence of diarrhea in children include the hand-washing behaviors of caregivers at 4 critical times (before cooking, after defecating, before feeding the child, before eating). An intermediate indicator for child malarial prevalence is the utilization of insecticide bed nets the previous night while sleeping.

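### The diarrhea model adjusts for caregiver hygiene and water quality, which the volunteers are meant to change, and so removes part of the effect on a primary endpoint

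*Protocol*

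**What the plan says.** Diarrhea prevalence in children under 5 is a primary endpoint (Protocol, Primary endpoint and Table 1). The Data analysis section opens with the analysis principle: "Intention-to-treat analysis will be conducted to explore the effect of CHV activation on childhood infectious disease". It then sets the covariates for this endpoint: "For diarrheal prevalence as a dependent variable, water quantity and quality, hygiene behavior of caregivers, presence of improved latrines", followed by child characteristics, household income and caregiver education. All of these "will be controlled for in quantifying the net effect of CHVs". The section does not say which survey round supplies the values.

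For malaria, the same paragraph takes the opposite line on an intermediate variable: "insecticide-treated bed net utilization will not be controlled since it is considered an intermediate factor between intervention and disease outcome".

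Three other statements bear on the point:

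- Intermediate indicators: "Intermediate indicators for the prevalence of diarrhea in children include the hand-washing behaviors of caregivers at 4 critical times". The next sentence there gives bed nets the same status: "An intermediate indicator for child malarial prevalence is the utilization of insecticide bed nets the previous night while sleeping".
- Key intervention: "CHVs conduct health education with key messages on sanitation and hygiene to prevent diarrhea and other infectious diseases such as hand-washing".
- Table 3, home-visit duties: "Provide Aquatabs to households without an appropriate source of drinking water".

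**The concern.** Randomization protects the comparison of the arms as allocated. A covariate measured after allocation and changed by the intervention is part of the result, not a baseline difference to be evened out. If volunteers persuade caregivers to wash their hands and fewer children then have diarrhea, comparing arms at equal levels of hand-washing discards that benefit. The coefficient for arm becomes a residual direct effect, although the section promises an intention-to-treat effect of activating the volunteers.

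This matters more for diarrhea prevalence than for most endpoints. ORS and zinc go to children who already have diarrhea, so prevention through hygiene and water is a main route by which the package can lower prevalence. The Discussion stresses that preventive role. A program that works as designed could therefore be reported as having little effect.

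There is a second problem. Follow-up hygiene and diarrhea share causes that were not randomized, such as household conditions and caregiver attention. Conditioning on hygiene lets those causes bias the comparison between arms.

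**Working it through.** **1. Consistency of the text.** The point is about covariate choice and rests on no figure stated in the protocol. The two models compare as follows.

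| | Malaria model | Diarrhea model |
|---|---|---|
| Variable | Bed-net use | Caregiver hygiene (hand-washing) |
| Status under Intermediate indicators | Intermediate | Intermediate |
| Taught by volunteers (Key intervention) | Yes | Yes |
| Treatment in Data analysis | Left out, because intermediate | Adjusted for, no reason given |

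Two variables with the same stated role get opposite treatment in one paragraph. Water quality is not listed as an intermediate indicator, but the Aquatabs duty in Table 3 makes it a target of the intervention in households without an appropriate source.

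**2. Illustration of the attenuation.** All inputs here are assumptions. Control prevalence is 20% (Table 2 shows 17.5% and 20.1% at the first round). The true risk ratio is 0.75, borrowed from the protocol's malaria assumption. Good hygiene is 30% in control and 60% in intervention. A share s of the log risk ratio runs through hygiene.

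- Unadjusted OR = (0.15/0.85)/(0.20/0.80) = 0.1765/0.25 = 0.71.
- The hygiene risk ratio r solves (0.4 + 0.6r)/(0.7 + 0.3r) = 0.75^s. The direct risk ratio is 0.75^(1−s).
- For s = 0.5, 0.75^0.5 = 0.866 and r = 0.606. The control risk without good hygiene is 0.20/(0.7 + 0.3 × 0.606) = 0.227.
- Without good hygiene the risks are 0.227 and 0.196 (OR 0.83). With good hygiene they are 0.137 and 0.119 (OR 0.85). The logistic model pools these to 0.84.

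| Share through hygiene | Unadjusted OR | Hygiene-adjusted OR |
|---|---|---|
| 0% | 0.71 | 0.71 |
| 10% | 0.71 | 0.73 |
| 30% | 0.71 | 0.78 |
| 50% | 0.71 | 0.84 |
| 70% | 0.71 | 0.90 |
| 100% | 0.71 | 1.00 |

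A second set of assumptions gives a similar picture. Take good hygiene in 30% and 50%, hygiene OR 0.5, direct OR 0.85, and 25% prevalence in control children without good hygiene. The arm prevalences are then 21.8% and 17.2%, so the total OR is 0.75 against an adjusted OR of 0.85. The part of the log odds ratio removed is 1 − ln(0.85)/ln(0.748) = 1 − 0.1625/0.2903 = 44%.

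**3. What this could mean for detection.** Pooled first-round prevalence is (175 + 192)/(999 + 957) = 18.8%. Other inputs are k = 0.16, 20 clusters per arm and 950/20 = 47.5 households per cluster (Sample size calculation). A two-sided 5% level is assumed because the protocol states none, and one child per household. With c clusters and m children per cluster,

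power = Φ{√[(c − 1)(p0 − p1)²/V] − 1.96}, where V = p0(1 − p0)/m + p1(1 − p1)/m + k²(p0² + p1²).

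| Relative reduction left after adjustment | p1 | V | Root term | Power |
|---|---|---|---|---|
| 25% (nothing removed) | 14.1% | 0.00716 | 2.42 | 68% |
| 18.75% (a quarter removed) | 15.2% | 0.00743 | 1.78 | 43% |
| 12.5% (half removed) | 16.4% | 0.00769 | 1.17 | 21% |

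These figures treat the attenuated effect as the one being tested. They ignore any change in standard error from adding covariates, and they do not apply the planned 10% loss to follow-up.

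**The case against.** The strongest objection is timing. A first-round survey came before allocation, and the protocol never says that follow-up values will be used. If the covariates are first-round values, no mediator is conditioned on and the harm disappears. An unseen analysis plan might say so. But the sentence on bed nets makes sense only if covariates are measured after the intervention starts, since a first-round value could not be an intermediate. Follow-up values are therefore the natural reading of the whole paragraph. If first-round values were intended, the text still needs to say so.

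Three further points stand in part:

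- **Direction.** Attenuation is expected if hygiene improves and protects, but it is not guaranteed. In a simulation with assumed inputs (direct OR 0.8, hygiene OR 0.8, an unmeasured risk factor), adjustment moved the arm OR from 0.76 to 0.81 without confounding. It moved to 0.73 when higher-risk households had four times the odds of practicing good hygiene.
- **Water quality is the weaker half.** It rests on one item in Table 3, limited to some households. If it is measured only as source type, as in Table 2, Aquatabs would not change it. For water quantity and latrines, general sanitation messages are the only visible link.
- **Reach.** Only the diarrhea model is affected. The fever, RDT and ORS indicators in Table 1 are not, and the sample size was set on malaria.

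None of this removes the contradiction over hygiene.

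**Conclusion.** The concern holds. As written, the diarrhea model adjusts for caregiver hygiene, which the protocol itself calls intermediate, and for water quality, which its volunteers are asked to improve. This contradicts the rule stated for malaria in the same paragraph, and under the natural reading it changes what is estimated for a primary endpoint. That internal contradiction is enough to require correction before analysis.

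The size cannot be known from the documents. It runs from nothing, if the volunteers do not change hygiene or water, to the whole effect, if they act only through them. In the main illustration the odds ratio moves from 0.71 to between 0.78 and 0.90 for mediated shares of 30% to 70%. The mediated share, the rise in hygiene and the risk ratio are all assumptions. The hygiene part of the finding is firm, the water-quality part is supported but secondary, and attenuation is the likely direction rather than a certain one.

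**What to change.** Replace the diarrhea covariate sentence in Data analysis with text to this effect:

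> *The primary diarrhea model will adjust for the age and sex of the child, household income and caregiver education. Hygiene behavior, water quantity and quality, and latrine status will enter, if at all, only at their first-round values. Models using values from later rounds will be reported as exploratory mediation analyses.*

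This applies the existing bed-net rule to both endpoints. Restricting all the water, hygiene and latrine variables to first-round values is safe even where the link to the intervention is weak: a pre-allocation value can still add precision and cannot absorb the effect. Any of these that the first-round survey did not record should simply be left out.

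The cost is one sentence. No new data are needed, and the follow-up measurements keep their use as intermediate indicators and in the process evaluation.

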**Methods**

***Study setting***

The Ketu South district is one of the 25 administrative districts in the Volta Region, located in the southeastern corner of Ghana (See Figure 1). The Ketu South district is a relatively low land area, with altitudes ranging from less than 15 meters at the coast to 66 meters inland. The 2010 Population and Housing Census recorded a total population of 160,756, with 52.9% of the population consisting of females. The projected population for the district for 2015 based on an annual growth rate of 2.5% is 181,881, with 36,376 children under 5 years of age. The people of Ketu South are the Ewe tribe, which inhabits some parts of Togo, Benin, and the Volta Region of Ghana. They are a patrilineal society governed by a hierarchical, centralized authority. The district is culturally homogenous, with negligible variations. According to the 2010 Population and Housing Census, Christianity accounts for 59.0% of the total population, followed by traditional religion (27.9%) and Islam (3.5%). The people living in the district are predominantly fishermen, fish mongers, petty traders, and weavers of *kente* (a specific type of silk and cotton fabric that originated in the Ashanti Empire), with a few government workers interspersed among the population.

Figure 1. Study area.

| [figure not shown] |
| --- |

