***Primary endpoint***

This study aims to assess the effect of CHVs on multiple child health outcomes. The primary endpoints of the study are the prevalence of diarrhea and fever/malaria among children under 5 years of age, and the proportion of children receiving case management for diarrhea and malaria. We plan to use the 14-day prevalence of reported diarrhea and the 14-day prevalence of fever/malaria in the household as indicated in caregiver’s reports.

For the case management for diarrhea, we will investigate whether a child with diarrhea has been administered ORS. For malaria, we will measure whether a child with malaria symptoms was tested using an RDT kit and whether he or she was referred to a health facility if diagnosed with malaria.

The survey will be conducted three times at the household level: the first and second round will be carried out in the first phase, and the final round will be carried out in the second phase.

Diarrheal is defined as 3 or more instances of watery stools within 24 hours over the last 14 days. Febrile episodes will be assessed as a proxy indicator of malarial prevalence based on caregiver reports.

The main outcomes and indicators are presented in Table 1.

Table 1. Main outcomes and indicators.

| **Indicator (%)** (Denominators are within the respondents of the household survey) | | |
| --- | --- | --- |
| Use of ORS among under-5 children with diarrhea | Numerator | Number of U5C^1^ who took ORS^2^ when experiencing diarrhea over the past 14 days |
|  | Denominator | Number of U5C who experienced diarrhea in the past 14 days |
| Prevalence of diarrhea in under-5 children | Numerator | Number of U5C who experienced diarrhea in the past 14 days |
|  | Denominator | Number of U5C |
| Diagnosis rate of malaria in under-5 children using an RDT | Numerator | U5C diagnosed with RDT for malaria in the last two weeks |
|  | Denominator | U5C who have complained of fever in the last two weeks |
| Malaria incidence in under-5 children | Numerator | U5C who have complained of fever in the last two weeks |
|  | Denominator | Number of U5C |

^1^ U5C, under-5 children; ^2^ ORS, oral rehydration solution

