***Eligibility criteria and randomization***

Forty communities were assigned into 8 strata on the basis of the prevalence of diarrhea in under-five children, economic status of the community, and the proportion of mothers who delivered their youngest child by a skilled birth attendant based on the results of the first-round survey. To evaluate the socioeconomic status of a community, we used the proportion of households with wattle and daub houses as representatives of the lowest economic level. We ensured that an equal number of communities within all 8 strata were randomly allocated into the intervention and control arms, with each arm including 20 communities. Microsoft Excel version 15.22 was used for randomization. We ensured comparability in the main outcomes between the intervention and control arms by strictly applying randomization. After conducting the first-round survey, we classified the clusters into strata by primary endpoint and socioeconomic status. In doing so, we were able to ensure a high comparability and therefore were able to avoid selection bias. Control communities are allocated by randomization among the target communities. We found control and intervention communities well balanced in terms of caregivers’ demographic and socioeconomic status, and child demographic status and several key variables related to primary outcomes of the intervention (Table 2).

Figure 2. Flow diagram of the trial.

| [figure not shown] |
| --- |

Table 2. Results of the first-round survey in the intervention and control arms.

| **Variables** | | **Intervention** | | **Control** | |
| --- | --- | --- | --- | --- | --- |
|  |  | N | % or  mean (SD^2^) | N | % or  mean (SD) |
| Caregiver's age (years) | | 999 | 29.00(7.16) | 957 | 28.86(6.78) |
| Religion of respondent | Christian | 614 | 61.50% | 599 | 62.60% |
|  | Traditionalist | 280 | 28.00% | 256 | 26.80% |
| Education level of respondent | Graduated basic school | 188 | 23.6% | 165 | 22.5% |
|  | Dropped out of basic school | 455 | 57.2% | 406 | 55.3% |
|  | Graduated secondary school | 19 | 2.4% | 24 | 3.3% |
| Possession of NHIS^1^ Card | Have a valid card | 332 | 33.2% | 328 | 34.3% |
| Age of the youngest child under-5 child (In months) | | 989 | 22.97 (15.95) | 946 | 21.97 (15.94) |
| Youngest child’s sex | Male | 505 | 50.6% | 483 | 50.5% |
| Main source of drinking water for the last-born child | Hand-dug well | 268 | 26.8% | 248 | 25.9% |
|  | Sachet water | 202 | 20.2% | 223 | 23.3% |

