One of the limitations of this trial is that malaria cases are not being confirmed using laboratory tests. We will measure fever reported by a caregiver as a proxy indicator of malaria prevalence in both arms of the trial. Although RDTs will be used to test for malaria in children with a fever, this will only be the case for households within the intervention arm since the testing will be conducted by CHVs. Despite its seasonal variance, fever, as the primary manifestation of malaria in young children, can be utilized as an indicator of malaria prevalence, although some source has suggested that it must be interpreted with caution [36].

The project team must start recruiting CHVs in control arm during the second phase and also reached an agreement with the local governments to commence CHV activation without any further delay right after the first phase regardless of any pronounced effects on children. If we have to implement CHV activation in the control arm, we cannot maintain two different arms with and without intervention, which means we cannot compare the outcomes of the intervention during this phase. Hence, we ruled out an optimization phase. We thus cannot consider an optimization phase for this trial although we think optimization is important.

Due to the absence of demographic data for the study district, we used estimated population figures for each community derived by the officials of the Ghana Health Service. However, during the baseline survey we found discrepancies between the estimated and actual number of households in communities, and these figures were adjusted during the sampling process in some communities. Although a pre-survey listing the households in each community is recommended to enhance the accuracy of household sampling, budgetary constraints prevented us from carrying out such a survey.

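### The fever model rules out season and altitude on a claim of balance that the protocol does not show and, for later survey rounds, cannot yet know

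*Protocol*

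**What the plan says.** The Data analysis section first accepts that the environment matters: "Environmental risk factors such as seasonality and altitude are also considered to be independent variables for malaria prevalence". It then closes the matter in the next sentence: "the intervention and control arms in our study site present no difference in those factors so there will be no control for environmental factors". This is a stated exclusion resting on a stated fact, not a detail left for a later document.

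Other parts of the protocol bear on that fact:

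- **Altitude.** Study setting describes a relatively low-lying district with "altitudes ranging from less than 15 meters at the coast to 66 meters inland". No altitude is given by arm or by community.
- **Season.** The Discussion concedes that the endpoint is seasonal: "Despite its seasonal variance, fever, as the primary manifestation of malaria in young children, can be utilized as an indicator of malaria prevalence".
- **Endpoint.** Primary endpoint uses "the 14-day prevalence of fever/malaria in the household as indicated in caregiver’s reports", so what a caregiver reports depends on the date of the interview.
- **Survey timing.** Rounds are placed by phase only: "the first and second round will be carried out in the first phase, and the final round will be carried out in the second phase". There are no calendar dates, and nothing says that both arms are visited in the same weeks.
- **Randomization.** "Forty communities were assigned into 8 strata on the basis of the prevalence of diarrhea in under-five children, economic status of the community", with skilled birth attendance as the third factor. Altitude and survey date are not used.
- **Table 2.** Neither altitude nor interview date is reported by arm.

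**The concern.** The protocol names two predictors of its outcome and then fixes their exclusion by asserting balance. The assertion has three weaknesses.

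1. Nothing shown supports it. The baseline table and the strata contain neither factor.
2. For season it cannot yet be known. Interview dates in later rounds depend on the order in which field teams visit communities, and randomizing communities does not set that order.
3. Balance is a poor reason to drop a prognostic covariate. Adjustment also removes outcome variation between communities, so it can help precision even when the arms match.

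Reported fever is the proxy for malaria prevalence, on which the trial is sized. If one arm were surveyed nearer the fever peak than the other, part of the seasonal difference would be read as an effect of the volunteers, or would hide one, and the stated model would not correct it.

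**Working it through.** **Planned effect.** Sample size calculation gives 25% prevalence and a 25% relative reduction: 25 x 0.75 = 18.75%, a difference of 6.25 points.

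**The plan's own figure.** The contested sentence contains no number, so the reference is the sample size. The coefficient-of-variation formula for cluster trials, with 5% two-sided alpha assumed because the protocol states none, is

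c = 1 + (1.96 + 0.84)^2 x [p0(1-p0)/m + p1(1-p1)/m + k^2(p0^2 + p1^2)] / (p0-p1)^2.

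With p0 = 0.25, p1 = 0.1875, k = 0.16 and m = 950/20 = 47.5, c = 20.4. This agrees with the stated 20 clusters per arm.

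**Season: slope of fever over time.** The protocol gives no seasonal figures. Assume a sinusoid over 52 weeks. Average slope = (high - low)/26 per week. Steepest slope = [(high - low)/2] x 2 x pi/52 per week.

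| Assumed swing | Average slope (points/week) | Steepest slope (points/week) |
| --- | --- | --- |
| 20% to 30% | 0.38 | 0.60 |
| 20% to 35% | 0.58 | 0.91 |

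**Case A: visit order unrelated to arm.** Assume a 6-week round, visits spread evenly and one date per community. The SD of a community's date is 6/sqrt(12) = 1.73 weeks. The SD of the gap between the arm means is 1.73 x sqrt(2/20) = 0.55 weeks. A 1-SD gap shifts the contrast by 0.55 x 0.38 = 0.2 points at the low end and 0.55 x 0.91 = 0.5 points at the high end, about 3% to 8% of 6.25.

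**Case B: mean dates 3 weeks apart.** For the 20-30% swing the shift is 1.15 points (average slope) to 1.81 (steepest). For 20-35% it is 1.73 to 2.72. The range is about 1.2 to 2.7 points, or 18% to 43% of 6.25. With evenly spread visits over T weeks, the largest possible gap between arm means is T/2, reached only if one arm is finished before the other starts. A 3-week gap therefore needs a round of at least 6 weeks, and in a 6-week round it needs complete separation of the arms.

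**Case C: both arms surveyed in the same weeks.** The gap is zero and so is the shift.

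**Altitude: chance imbalance.** If 20 of the 40 communities were low-lying (assumed) and allocation were simple, a 12:8 split or worse would occur with probability 0.34, and 13:7 or worse with probability 0.11. The protocol gives no altitude effect on fever, so this cannot be turned into points.

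**Precision.** Use m = 47.5 x 0.9 = 42.75 after 10% loss, with k = 0.16 and the formula above. Power is 76.0% with no between-community variance removed, 78.5% if 25% is removed and 81.1% if 50% is removed. Those shares are assumptions. The gain is about 2 to 5 percentage points of power.

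**The case against.** The case for leaving the plan alone is substantial, and most of it stands.

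- **Altitude.** It is fixed before randomization, and communities were randomized within strata. Omitting it is valid and leaves only chance imbalance, which the planned cluster-level analysis reflects in its standard errors. The documented range is narrow and covers the whole district. Urban areas were excluded, so the spread among trial communities is unknown.
- **First round.** Allocation used the first-round results, so those interviews could not have been scheduled by arm.
- **Later rounds.** The same rounds cover both arms in one district. If the authors mean that both arms share a climate, that is reasonable. What may differ is the interview date.
- **Wording.** The sentence sets the covariates of the model. It does not bar a sensitivity analysis. The map and the flow diagram are not shown here, so indirect support for similar geography cannot be excluded.

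Two stronger readings are tempting. A reader might infer that the fever comparison is biased by 18% to 43% of the planned effect. The documents do not support this: it needs an assumed seasonal swing and near-complete separation of the arms in time, and no text says or implies that separation.

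A reader might also take the first-round fever gap in Table 2 as proof that the arms differ in season or altitude. It was 29.4% against 35.2%, that is 5.8 points or 93% of 6.25. It shows only that the arms differed on fever before the intervention. Nothing links the gap to either factor.

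What the objection does not answer is that the stated reason is unsupported, cannot be known in advance for season, and would not justify the exclusion if true.

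**Conclusion.** The point holds in a limited, conditional form and is minor. The rule rests on a premise that no shown text or table supports. Its consequences differ by factor:

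- **Altitude:** some lost precision and uncorrected chance imbalance, without systematic bias.
- **Interview date:** bias only if the arms are surveyed at different times in a later round, which the protocol neither states nor prevents.

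The size cannot be fixed from the documents. Under the assumed swings, the ordinary case is a shift of a few tenths of a point. A shift of more than a point needs the arms to be weeks apart. The precision gain from adjustment is modest at the planned coefficient of variation and depends on how much between-community variance the two factors explain.

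**What to change.** Delete the sentence that rules out control for environmental factors. Prespecify two further covariates in the fever model: interview date, as calendar month or fortnight, and community altitude. In the later rounds, order the visits so that intervention and control communities are surveyed in the same weeks. That order must be set before fieldwork, because adjustment for date does little if the arms hardly overlap in time.

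The cost is small: two more covariates, one altitude value per community, an interview date on each survey form, and some constraint on the visit order. No extra households are needed.
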